## Abstract

**Background:**

Work-related stress is one of the top sources of stress amongst working adults. Relaxation rooms are one organizational strategy being used to reduce workplace stress. Amongst healthcare workers, relaxation rooms have been shown to improve perceived stress levels after 15 min of use. However, few studies have examined physiological and cognitive changes after stress, which may inform why relaxation rooms reduce perceived stress. Understanding the biological mechanisms governing why perceived stress improves when using a relaxation room could lead to more effective strategies to address workplace stress.

**Objective:**

The purpose of this research study is to understand how physiological measures, cognitive performance, and perceived stress change after acute stress and whether certain sensory features of a relaxation room are more effective at promoting recovery from stress.

**Methods:**

80 healthy adults will perform a stress induction task (Trier Social Stress Test, TSST) to evaluate how physiological and cognitive responses after stress are affected by sensory features of a relaxation room. After the stress induction task, participants will recover for 40 min in a MindBreaks™ relaxation room containing auditory and visual stimuli designed to promote relaxation. Participants will be randomized into four cohorts to experience auditory and visual stimuli; auditory stimuli; visual stimuli; or no stimuli in the room. Measures of heart rate and neural activity will be continuously monitored using wearable devices. Participants will perform working memory assessments and rate their perceived stress levels throughout the experiment. These measures will be compared before and after the stress induction task to determine how different sensory stimuli affect the rate at which individuals recover.

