## Materials and Methods

### Recruitment

At the onset of the study, 20 healthy participants above the age of 18 will be recruited during which study parameters will be optimized. Results from these participants will be used to optimize the duration of baseline and recovery epochs of the experiment. After establishing the study parameters, 80 healthy participants will be recruited and randomly assigned into one of four cohorts (20 participants per cohort) as depicted in Figure 1. Cohorts will be randomized and stratified across sex and age, as these factors have been shown to affect physiological responses after stress (Labuschagne et al., 2019; Narvaez Linares et al., 2020). Randomization will be similar to quantitative randomized controlled trials as described by Hong and colleagues (Hong et al., 2018). All participants recruited and consented before the start of the study will be randomized using random assignments generated by a computer to stratify the median age and male/female ratios between cohorts. Any remaining participants recruited after the start of the study will be randomized using block randomization (computer randomized block lengths of 4) to balance the median age and male/female ratios across cohorts consistent with covariate adaptive randomization techniques (Suresh, 2011). Although not directly controlled for in the randomization, we will also ask participants about their job information such as position, length of employment, and perceived workplace stress to be able to characterize with their stress responses during the TSST in exploratory, *post hoc* analyses. Participants mainly will be recruited from a major healthcare organization, however there will be no requirement that participants be healthcare professionals due to the time commitment of the experiment (3 h from approximately 1PM to 4PM).

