### Cognitive Assessments

Participants will perform cognitive assessments to assess working memory function at specific times during the stress induction task. Acute stress has been shown to affect performance on working memory tasks (Vedhara et al., 2000; Shields et al., 2016; Jiang and Rau, 2017). In this study, participants will use a cognitive assessment application designed by the Well Living Lab (Jamrozik et al., 2019; Aristizabal et al., 2021a) to perform two working memory tasks: the Operation Span (OSPAN) task and the Symmetry Span (SSPAN) task (Foster et al., 2015; Draheim et al., 2018). Participants will perform these assessments on a 12.9” iPad Pro (*Apple Inc., California, United States*) located on a desk to ensure consistent placement across participants. Although some studies have required 85% accuracy on the processing components of the task (math accuracy for OSPAN, symmetry accuracy for SSPAN), other studies have found similar task performance measures without requiring such a processing accuracy threshold (Đokić et al., 2018). To ensure we have cognitive measures for each time step in the TSST (outlined in Figure 2), we will not require a processing accuracy threshold when analyzing changes in cognitive performance.

Two dependent measures will be used for analysis of both SPAN tasks: Unit Score and Load Score. The Unit Score is the average of the proportion of letters or grids participants can recall correctly in the appropriate order in each set. The Load Score is calculated from the sum of correctly recalled elements from all trials, regardless of the order. Both scores will be used to assess changes in working memory capacity before and after the stress induction task.

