#### Power Analyses

Sample size was determined based on the 5 cognitive performance measures, which were the least frequent measure collected during each experimental session, with an assumption of using a univariate mixed effects model with 5 measurements per participant, significance level of 0.05, moderate correlation between repeated measures (0.3), and directly comparing two experimental conditions instead of all conditions at once. Powering based on the least frequent measure ensured that we were sufficiently powered when analyzing the other measures in the study. We would reach 80% power with 18 participants per group with a mean difference of 1 standard deviation. Including 20 participants per group will provide a buffer for potential drop-out.

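### Cohort comparisons are described as before versus after stress; stating that they adjust for each participant's pre-stress baseline, and for sex and age, would protect power at almost no cost

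*Protocol article*

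**What the plan says.** The Abstract (Methods) states: "These measures will be compared before and after the stress induction task to determine how different sensory stimuli affect the rate" at which people recover. Cognitive Assessments says of the two span scores: "Both scores will be used to assess changes in working memory capacity before and after the stress induction task". The sections on cardiac measures and neural activity compare HRV indices and alpha power before, during and after stress. The Introduction's hypothesis is a faster return to pre-stress levels.

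Planned Statistical Analyses names univariate mixed-effects models for cognitive and survey outcomes, and GEEs comparing epochs for the physiological outcomes. It gives no model formula and mentions no covariates.

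Two design features bear on this:

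- The Trier Social Stress Test Protocol section puts all participants in the control condition for a 30-minute baseline before the stressor.
- Recruitment states: "Cohorts will be randomized and stratified across sex and age, as these factors have been shown to affect physiological responses after stress".

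Power Analyses assumes a "univariate mixed effects model with 5 measurements per participant", a 0.05 significance level and a correlation of 0.3 between repeated measures, "directly comparing two experimental conditions instead of all conditions at once". It concludes: "We would reach 80% power with 18 participants per group with a mean difference of 1 standard deviation".

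**The concern.** Throughout, the baseline appears as one level of a comparison and never as a covariate. Naming a mixed model or a GEE does not settle the matter. If such a model gives each cohort its own baseline mean and tests cohort by epoch, the test has the variance of a change score. When the correlation between occasions is below 0.5, as the plan assumes, subtracting baseline adds more noise than it removes, so a change score is less precise than the post-stress value alone.

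Nothing in the design calls for that loss. Cohorts are randomised and share the same baseline condition, so their baseline means differ only by chance. A baseline covariate or a common baseline mean is therefore justified. For the same reason, a pre-stress assessment cannot carry a cohort effect. The Discussion confirms that cognitive tasks are done at baseline. Precision matters here because only 20 participants are planned per cohort.

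**Working it through.** **Inputs.** From Power Analyses: difference 1 SD, correlation ρ = 0.3, significance level 0.05, 80% power, 18 per group analysed and 20 enrolled, two cohorts compared at a time. Assumed: a two-sided test (sidedness is not stated), equal variances, and the same ρ between all pairs of occasions.

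**The plan's own figure.** With V the variance of the per-participant summary in SD² units, n per group ≈ 2V(1.96 + 0.84)² ≈ 15.7V by the normal approximation. The t version adds about one.

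- Single post-stress occasion, V = 1: 16 (normal) or 17 (t).
- Difference in linear change totalling 1 SD over five equally spaced measures, V = 16(1 − 0.3)/10 = 1.12: 18 (normal) or 19 (t).
- Mean of all five measures, V = (1 + 4 × 0.3)/5 = 0.44: 7 or 8.
- Single change score, V = 2(1 − 0.3) = 1.40: 22 or 23.

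The stated 18 lies within two of both of the first two contrasts. The article does not say which contrast was used, so this match does not identify the method.

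**One pre and one post value, ρ = 0.3.** Formulas for V: change 2(1 − ρ) = 1.40; post only 1; baseline-adjusted 1 − ρ² = 0.91. Power comes from the noncentral t distribution with noncentrality 1/√(2V/n). At n = 18 this is 2.54, 3.00 and 3.14 respectively.

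| Contrast | V | n per group for 80% (t) | Power at 18 | Power at 20 |
|---|---|---|---|---|
| Change score | 1.40 | 23 | 69% | 74% |
| Post only | 1.00 | 17 | 83% | 87% |
| Baseline-adjusted | 0.91 | 16 | 86% | 90% |

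Adjustment cuts the variance by 1 − 0.91/1.40 = 35% relative to the change score. The adjusted row ignores the small extra variance from estimating the slope on baseline.

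**Other correlations, 18 per group.** At ρ = 0.5 (V = 1.00 against 0.75), power is 83% for change and 92% adjusted. At ρ = 0.7 (0.60 against 0.51), it is 96% and 98%. The gap narrows but the order does not change.

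**Several post values averaged, ρ = 0.3, 18 per group.** For the mean of k post values minus one baseline, V = (1 + (k − 1)ρ)/k + 1 − 2ρ.

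- k = 2: V = 0.65 + 0.40 = 1.05, power 81%.
- k = 3: V = 0.533 + 0.40 = 0.933, power 86%.
- k = 4: V = 0.475 + 0.40 = 0.875, power 88%.

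With baseline adjustment at k = 4, V = 0.475 − 0.09 = 0.385 and power is 99.7%.

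**Sex and age.** The article does not say how much variance they explain. If they explain none, adding both to the baseline-adjusted model at 18 per group moves power from 86.3% to 86.1%, a cost of 0.2 points. If they explained 20% of the residual variance (an assumption), power would be about 93%.

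**The case against.** The strongest reply is that the article never commits to a change score. The Abstract sentence asks about the rate of recovery, and the analysis section names mixed models and GEEs, either of which can carry baseline as a covariate or hold the baseline mean common across cohorts. Covariate lists normally sit in a full protocol or analysis plan, which is not shown here, so their absence alone is no fault. Comparing with the pre-stress level also follows from a hypothesis about return to that level.

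All of this stands. It means the loss is conditional on how the models are set up. It does not remove the point, because the contrast that the article does describe, repeatedly, is before/after or across epochs. Left unconstrained, that contrast is the inefficient one.

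A reader might go further and infer that the trial misses its 80% power. The documents do not support that. The 69% belongs to one pre and one post value, which the article does not name as the powered contrast. A change-type contrast already passes 80% once two post values are averaged. The timeline figure that would show how many of the five assessments follow the stressor is not available.

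A reader might also infer that leaving out sex and age inflates standard errors by a known amount. That would need a figure for explained variance, which the article does not give. Recruitment ties these factors to physiological responses, whereas the power calculation concerns cognitive measures. In a within-person contrast, additive effects of sex and age on level cancel anyway.

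**Conclusion.** The point holds as a low-cost improvement to the stated comparison. It is not an error in the sample size: 18 per group is roughly reproducible and is not shown to be wrong.

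If the cohort-by-epoch contrast leaves baseline means unconstrained, it gives up about 17 points of power relative to baseline adjustment with one pre and one post value (69% against 86% at 18 per group). With four post values averaged, the gap is about 12 points (88% against 99.7%). These sizes rest on the plan's ρ of 0.3, a 1 SD difference, an assumed two-sided 0.05 and equal correlation between occasions. They shrink as ρ rises. All the gain shown comes from baseline; the gain from sex and age cannot be quantified from the article.

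**What to change.** State in the analysis section that, for every between-cohort comparison:

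- recovery-epoch values are modelled with the participant's own baseline-epoch value as covariate, or with a mixed model or GEE that holds the baseline mean common across cohorts;
- sex and continuous age, the factors balanced at randomisation, are included;
- the baseline assessment does not carry a cohort effect.

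Keep the within-person before/after comparisons for describing return to baseline. No new data or participants are needed: baseline measures, sex and age are already part of the design. The cost is the wording and a few degrees of freedom, with about 0.2 points of power lost if sex and age prove uninformative.

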**Results:**

Recruitment started in December 2021 and will continue until December 2022 or until enrollment is completed. Final data collection and subsequent analysis are anticipated by December 2022. We expect all trial results will be available by early 2023.

**Discussion:**

Findings will provide data and information about which sensory features of a relaxation room are most effective at promoting recovery after acute stress. This information will be useful in determining how these features might be effective at creating individualized and organizational strategies for mitigating the effects of workplace stress.

## Introduction

According to the 2021 Stress in America™ survey, work-related stress is the top source of stress amongst adult workers (American Psychological Association, 2021). Suboptimal workplace conditions, lack of resources and autonomy, unsupportive interpersonal relationships, and excessive workloads have each been identified as contributors to negative physical and mental health (Danna and Griffin, 1999). Healthcare is one profession that is heavily affected by workplace stress and burnout (Hoff et al., 2017; Dyrbye et al., 2019a,b, 2021; National Academies of Sciences Engineering Medicine, 2019; Shanafelt et al., 2019). Clinician burnout affects quality and safety, patient-clinician relationships, productivity, and clinician turnover (West et al., 2018; National Academies of Sciences Engineering Medicine, 2019). Burnout also costs the U.S. healthcare system in excess of $4.6 billion each year (Han et al., 2019). Across professions, several interventions have been tested to mitigate the effects of burnout and workplace stress at both the individual and organizational level (West et al., 2016; Panagioti et al., 2017). Individual-focused interventions (e.g., meditation, yoga, and focused breathing), and organizational strategies (e.g., institutionally funded counseling sessions, mindfulness-based education courses, and stress management programs) can reduce burnout and workplace stress (Hätinen et al., 2007; Lambert and Corpus, 2021; Rolling et al., 2021; White et al., 2021). In the past few years, relaxation rooms have been used as an organization-level approach to reduce workplace stress and burnout. Relaxation rooms are designed to reduce stress (Ruotsalainen et al., 2015; Sass, 2019; White et al., 2021), however, certain features of the rooms might be more effective at reducing stress for one person than another.

The efficacy of relaxation rooms is often determined based on self-report of stress by the individual (Sass, 2019; Sullivan et al., 2019; Putrino et al., 2020; White et al., 2021). Recently, Putrino et al. (2020) found healthcare workers who used their multisensory, nature-inspired recharge room experienced a 59.6% reduction in self-reported stress levels after a single 15-minute session. However, improvements in perceived stress might not always align with changes in physiological or cognitive responses (Guyon et al., 2020; Loch et al., 2020). Understanding how features of a relaxation room affect physiological responses and cognitive function, in addition to perceived stress levels, could lead to a more individualized approach to reducing workplace stress and burnout.

Wearable devices are one approach to measuring an individual’s physiological responses (Can et al., 2019). Acute stress has been shown to increase heart rate (Kirschbaum et al., 1993) and increase self-report of stress and anxiety (Aristizabal et al., 2021b). Neural activity recorded using electroencephalography (EEG) has been shown to detect changes in spectral power during different epochs of a stress induction task. In a systematic review, Vanhollebeke and colleagues found alpha power has been shown to decrease in the presence of a stressor, which was not found in other frequency bands (Vanhollebeke et al., 2022). In recent years, wearable devices have been developed to allow for mobile EEG recordings to study how neural activity changes in response to stress (Schlink et al., 2017) or to different sensory stimuli (Mazurek et al., 2019). Studies have also shown that measures of cognitive performance are impacted by stress (Vedhara et al., 2000; Shields et al., 2016; Jiang and Rau, 2017). However, few studies have looked at how features of a relaxation room affect physiological measures and cognitive function after stress.

Prior studies have demonstrated naturalistic sensory stimuli are effective at promoting recovery after stress (Yin et al., 2020). Experiencing visual and auditory elements from nature has been shown to reduce stress and improve mood (Shibata and Suzuki, 2004; Fuller et al., 2007; Park et al., 2009; Brown et al., 2013; Hedblom et al., 2019). Physiological benefits in relation to heart rate and neural activity also occur after experiencing naturalistic visual and auditory stimuli (Jo et al., 2019; Yin et al., 2020). Cognitive performance has also been shown to be adversely affected by stress but can be improved when exposed to biophilic environments (Shields et al., 2016; Yin et al., 2018). Taken together, we hypothesize that physiological measures and cognitive performance after a stressful event will return to pre-stress levels faster when experiencing both auditory and visual stimuli of the MindBreaks room compared to only auditory or visual stimuli or neither.

The objective of this study protocol is to determine whether different visual and/or auditory features of a relaxation room affect the recovery of physiological signals, cognitive function, and perceived stress after an experimentally controlled acutely stressful event. Understanding how different sensory features promote recovery after stress could lead to an individual- and organization-level approach for using relaxation rooms to mitigate the effects of workplace stress and burnout.

## Materials and Methods

### Recruitment

At the onset of the study, 20 healthy participants above the age of 18 will be recruited during which study parameters will be optimized. Results from these participants will be used to optimize the duration of baseline and recovery epochs of the experiment. After establishing the study parameters, 80 healthy participants will be recruited and randomly assigned into one of four cohorts (20 participants per cohort) as depicted in Figure 1. Cohorts will be randomized and stratified across sex and age, as these factors have been shown to affect physiological responses after stress (Labuschagne et al., 2019; Narvaez Linares et al., 2020). Randomization will be similar to quantitative randomized controlled trials as described by Hong and colleagues (Hong et al., 2018). All participants recruited and consented before the start of the study will be randomized using random assignments generated by a computer to stratify the median age and male/female ratios between cohorts. Any remaining participants recruited after the start of the study will be randomized using block randomization (computer randomized block lengths of 4) to balance the median age and male/female ratios across cohorts consistent with covariate adaptive randomization techniques (Suresh, 2011). Although not directly controlled for in the randomization, we will also ask participants about their job information such as position, length of employment, and perceived workplace stress to be able to characterize with their stress responses during the TSST in exploratory, *post hoc* analyses. Participants mainly will be recruited from a major healthcare organization, however there will be no requirement that participants be healthcare professionals due to the time commitment of the experiment (3 h from approximately 1PM to 4PM).

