### MindBreaks Relaxation Room

A MindBreaks relaxation room will be used for this study to determine how the auditory and visual stimuli of the room affect physiological measures, cognitive performance, and self-report of stress during the recovery epoch of the Trier Social Stress Test (see section “Trier Social Stress Test Protocol”). The MindBreaks room is designed to deliver short, effective, and restorative breaks to help increase energy, reduce stress, enhance mood, improve focus, and boost performance (MindBreaks, 2022). The room contains biophilic visual stimuli in the form of an artificial green wall and plants, calming lighting, and a virtual nature skylight to promote relaxation and reduce stress (Berto, 2014; An et al., 2016; Wooller et al., 2018; Hedblom et al., 2019). Immersive natural auditory stimuli from the MindBreaks audio library are played in the room through Sonos^®^ speakers (*Sonos Inc., California, United States*) to provide a calming and relaxing experience (Alvarsson et al., 2010; Largo-Wight et al., 2016; Wooller et al., 2018). For this study, participants will experience the auditory and visual stimuli, auditory stimuli only, visual stimuli only, or no stimuli (control condition), depending on the cohort. Participants who do not experience the biophilic visual stimuli will see neutral curtains covering the walls of the room.

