### Trier Social Stress Test Protocol

Participants will perform the Trier Social Stress Test (TSST) to induce an experimentally controlled acutely stressful event (Kirschbaum et al., 1993). The TSST is a widely used laboratory procedure that places participants in a socially evaluative situation that reliably induces mental stress and elicits measurable physiological stress responses (Birkett, 2011). The experimental session is divided into three different epochs: (1) baseline (waiting period upon arrival), (2) stress induction task, and (3) recovery. During the baseline epoch, participants will rest for 30 minutes in the control condition (no biophilic visual or auditory features) to stabilize physiological responses and acquire baseline stress levels. During the stress induction task, participants will perform the TSST which consists of three 5-min phases: (1) the preparation phase, (2) the presentation phase, and (3) the mental arithmetic phase. During the preparation phase, the participant is asked to imagine they have applied for their dream job and given writing materials to make notes about what makes them the ideal candidate. During the presentation phase, the participant will argue why they are the best candidate for the job in front of an interview panel and while being recorded with a video camera and microphone. During the mental arithmetic phase, participants are asked to count backward by 13 starting from 1,022. During the recovery epoch, participants will rest in the MindBreaks room for 40 min while experiencing one of four conditions: auditory-visual stimuli, auditory stimuli, visual stimuli, or control condition (no stimuli). Previous studies have used different durations for each of these epochs (Narvaez Linares et al., 2020). Here, we will adjust the baseline and recovery epoch durations based on how quickly physiological signals and cognitive performance recover during the study optimization period involving 20 participants. Figure 2 depicts a timeline of the different epochs of the TSST, including the times when participants will be asked to perform the cognitive assessment tasks and fill out stress and anxiety self-reports.

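### One disclosed block length of 4 for four equal cohorts makes the last place in each block certain, and the text does not say that these blocks run within the sex and age strata that balance would need

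*Protocol article*

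**What the plan says.** All on this point is in the protocol article.

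- **Recruitment, design:** participants are "randomly assigned into one of four cohorts (20 participants per cohort"), 80 in all. A general statement follows: "Cohorts will be randomized and stratified across sex and age".
- **Recruitment, those consented before the start:** they "will be randomized using random assignments generated by a computer to stratify the median age and male/female ratios between cohorts".
- **Recruitment, everyone later:** they will be "randomized using block randomization (computer randomized block lengths of 4) to balance the median age and male/female ratios across cohorts". One length, 4, is given. The stated purpose is balance in median age and sex ratio, and the step is described as in line with covariate-adaptive techniques. The number of participants in this second group is not given.
- **MindBreaks Relaxation Room:** the conditions differ in sight and sound. For example, "Participants who do not experience the biophilic visual stimuli will see neutral curtains covering the walls of the room".
- **Trier Social Stress Test Protocol:** "During the baseline epoch, participants will rest for 30 minutes in the control condition". The stress task is described once, for all participants. The cohorts therefore differ only from the recovery epoch onward.

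**The concern.** Two features of the stated rule cause trouble.

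**Predictability.** The block length equals the number of cohorts and is published. Someone who has seen the earlier assignments in a block can narrow down the next one and, at the fourth place, know it. The risk is mainly in enrolment and scheduling: who is booked into the next slot could depend on the cohort expected there. Foreknowledge could also colour how staff treat a participant before recovery begins, in a trial that relies partly on self-reported stress.

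**Balance.** The stated aim of the block step is balance in age and sex, which the article says affect the physiological response to stress. Permuted blocks equalise cohort sizes. They balance a covariate only when run separately within levels of it. The text mentions strata, blocks and covariate-adaptive methods without saying how they combine. If the blocks are not within strata, a chance sex or age difference at 20 per cohort could be read as an effect of the room.

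**Working it through.** The article gives no figure on this point to reproduce.

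**Inputs from Recruitment:** four cohorts, 20 each, block length 4, applied to those recruited after the start (number unknown, so anywhere from 0 to 80).

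**1. Predictability within one block.** With equal allocation, each complete block is a random order of the four cohorts. For someone who knows the earlier places:

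| Place in block | Cohorts still possible | Chance of a correct guess |
|---|---|---|
| 1 | 4 | 1/4 |
| 2 | 3 | 1/3 |
| 3 | 2 | 1/2 |
| 4 | 1 | 1 |

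Average = (1/4 + 1/3 + 1/2 + 1)/4 = 2.083/4 = 52.1%, against 25% by chance. Simulation gives 52.2%. One assignment in four is certain. If all 80 were blocked without strata, that would be 80/4 = 20 assignments. This is a ceiling, because an unstated share is assigned by the other method.

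**2. What varying lengths would do.** In simulated lists of 80, an observer who knows all earlier assignments but not the block lengths guesses the cohort with the fewest so far:

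| Block lengths | Correct guesses |
|---|---|
| 4 only | 52% |
| 4 and 8 mixed | 48% |
| 4, 8 and 12 mixed | 46% |
| 8 and 12 mixed | 45% |

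The gain in average guessing is modest. The larger change is that, with undisclosed lengths, the last place is no longer known for certain.

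**3. Balance.** Assumptions not in the documents: all 80 go through the blocks, 50% are men, age is uniform from 18 to 65, and strata are sex by two age halves.

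| Method | Mean gap in number of men, highest minus lowest cohort | Mean gap in median age |
|---|---|---|
| Equal-size random allocation, no blocks | 4.61 | 10.2 years |
| Blocks of 4, no strata | 4.57 | 10.0 years |
| Blocks of 4 within strata | 1.19 | 4.6 years |

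With 30% men the gaps in number of men are 4.20, 4.15 and 1.20. Unstratified blocks do no better on sex or age than equal-size random allocation, while blocks within strata do much better.

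**4. Size of the sex gap in the unstratified upper-end case.** Take the number of women per cohort as Binomial(20, 0.5), independent across four cohorts. The gap between the most and least female cohort is at least 5 of 20 (25 percentage points) in 48% of allocations, and at least 6 of 20 in 30%. Fixing the total at exactly 40 women gives 49% and 31%.

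**The case against.** The strongest reply is that the scheme is not blocking alone. Recruitment says that the cohorts are stratified by sex and age, and participants consented before the start get a computer assignment aimed at that balance. If the later blocks also run within strata, the stated balance is broadly achievable. A reader might infer that the scheme cannot balance sex and age, but the document does not support that. It supports only that the text does not connect the blocks to the strata. The imbalance figures describe an upper-end case, not the trial as planned.

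A reader might also infer that staff will know the next cohort. The article does not say who prepares the room, who schedules sessions or who sits on the panel. Its silence on concealment and blinding may be condensation and is not a fault in itself. That someone delivering visibly or audibly different rooms learns past assignments is a fair inference and no more. Biased panel conduct also needs knowledge of the current participant's cohort. If the room is prepared early, staff have that knowledge under any block length.

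Two further readings should not be pressed. The phrase about block lengths may mean a random order within blocks of 4, so it is loose wording rather than a clear contradiction. A median age that changes during recruitment is no defect, since adaptive methods work with running values.

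What survives is the stated length itself, which equals the number of cohorts, and a description in which blocks, strata and covariate-adaptive methods are not reconciled. Stratifying does not remove the first problem: the last place in each stratum's block is still certain to someone tracking that stratum.

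**Conclusion.** The point holds within limits. For participants recruited after the start, the single disclosed length of 4 makes every fourth place in a complete block certain, and average best-guess success about double the chance level, for anyone who knows the earlier assignments. This rests on equal allocation, which is stated, and on someone having that knowledge, which is inferred. The number of participants affected is unknown. The Discussion expects main-trial recruitment to run from March to December 2022, so the group could be large.

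On balance, the finding is an unreconciled description rather than a demonstrated failure. Blocks within strata would largely deliver the stated aim, though they would be stratified blocking and not a covariate-adaptive method. Unstratified blocks would not deliver it. The 48% chance of a gap of at least 5 of 20 in women assumes no strata, all 80 participants in blocks and 50% women. The actual figure should be lower, because those consented before the start are assigned by a method meant to balance sex and age.

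The change is worth making because it is cheap and concerns a rule the article states, not detail it leaves out.

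**What to change.** 1. State one method that delivers the aim. Either use permuted blocks within sex by age-group strata with a fixed age cut, or use minimisation on sex and age with a random element. Call the first stratified blocking; only the second is covariate-adaptive.
2. If blocks are kept, let the length vary at random among multiples of 4 (for example 4 and 8), and do not disclose the lengths to session staff.
3. Open each assignment only after the stress task has started, and only to the person preparing the room. Baseline and stress task are the same in every cohort, so nothing before recovery needs the assignment. This is the more important step: it keeps the current cohort from the panel and the participant during stress induction. To limit guessing as well, past assignments should stay with that person.

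**Cost:** a regenerated list, slightly less exact cohort sizes at any moment, and a short window to set up the room. The stress task has three 5-minute phases, so 3 × 5 = 15 minutes; whether curtains, lighting and sound can be ready in that time should be tested beforehand.
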